### Data collection

#### Baseline

Baseline data are derived from lung function measurements and the interviews and questionnaires completed at inclusion.

The data is sampled online by social nurses using a smartphone or tablet, and the data is directly entered into REDCap (Research Electronic Data Capture) [19]. Further, the results of the spirometry are uploaded directly from the smartphone to REDCap.

If online data entry is not possible, a paper version of the survey will be available. At the end of the inclusion period, they will be sent to the Department of Clinical Research at Hvidovre Hospital and entered manually into REDCap.

Upon reaching the necessary number of participants, the local investigators will refer to the outpatient bookings and physician notes in the electronic patient record, to determine whether the participants underwent further evaluation at a department of respiratory medicine and if a diagnosis of COPD was confirmed (as indicated by ICD10 coding J44).

#### Five-year follow-up

Follow-up at 5 years will be performed using the unique civil registration number (Central Person Register (CPR) number) [20] through linkage to national Danish registers. A CPR number is a unique personal identification number assigned to all residents in Denmark. The CPR number consists of a unique 10 digits and includes information about the person’s date of birth.

Data on healthcare utilisation and hospital contacts in the cohort will be obtained from the Danish National Patient Register (NPR), and mortality data will be obtained from the Cause of Death Register. Data on redeemed prescriptions for COPD medication will be obtained from The Danish National Database of Reimbursed Prescriptions.

Patients’ labour market attachment and income basis are based on extractions from the Register-based Labour Force Statistics (RAS), administered by Statistics Denmark. Data on the highest acquired level of education (HFAUDD) will be obtained from Statistics Denmark.

The CPR numbers and collected survey data from REDCap for the study participants are transferred to Statistics Denmark (DST), where they are combined with information from the Danish National Patient Register, the Cause of Death Register, and the Danish National Database of Reimbursed Prescriptions. Data processing at DST is conducted using pseudonymized data within a secure server environment.

### Variables

#### Self-reported demographic variables

Demographic variables included sex and age at inclusion. The development of COPD is strongly associated with age and will be presented as a categorical variable in the following categories: 18–24, 25–34, 35–44, 45–54, 55–64, 65–79, 80+ years.

The categories for the highest completed education are divided into the following: incomplete primary school, primary school (completed 9th or 10th grade), high school/gymnasium, vocational education, tertiary education (short/2 years, medium/3–4 years, and long/5–6 years).

The indicator regarding attachment to the labour market is divided into three categories: employed, unemployed, and out of the workforce.

Housing conditions are included to describe the degree of vulnerability and include questions related to housing situation, type of housing/rough sleeping and whether they live alone or with others.

Symptom burden and impact on quality of life in patients diagnosed with COPD is evaluated using the COPD Assessment Test (CAT) [21], a validated questionnaire specifically designed to assess various aspects of their daily respiratory symptoms and limitations in daily activities.

#### Self-reported variables related to health risk assessment

Smoking status is evaluated based on the following categories: never smoked, former smoker, occasional smoker, and current smoker. The patients’ desire to quit smoking is self-reported.

Alcohol use is assessed by the AUDIT-survey (Alcohol Use Disorder Identification Test) developed by WHO [22].

Drug use is defined as attending substance maintenance treatment or reported use of other substances.

#### Clinical variables

The patients enrolled in this study may be categorized into four groups according to their diagnostic status: those previously diagnosed with COPD (self-reported), those identified as having COPD through screening, those without COPD as determined by screening, and those with an unknown diagnostic status due to insufficient lung function test. COPD identified through screening refers to people whose post-bronchodilator FEV1/FVC ratio is less than 0,7, according to the measurements obtained by the social nurse.

When assessing the prevalence of COPD, the groups diagnosed through screening and self-reported COPD are considered. Participants who are unable to perform spirometry are classified as having an unknown diagnostic status and are not included in the calculation of COPD prevalence.

At the 5-year follow-up, the prevalence of patients diagnosed with COPD after screening is identified either through the National Patient Health registry based on the ICD10 code J.44 or by examining prescriptions for COPD medication (including all types of inhalation medicine) recorded in The Danish National Prescription Database.

The utilization of healthcare services is evaluated based on all hospital contacts, including outpatient visits, admissions, and emergency department (ED) visits.

Admission diagnosis and department will be included as descriptive variables - partly to ascertain whether there are patterns in where the screening has the greatest impact, and partly to assess whether there is selection bias in the study.

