### Study subjects

The goal of this study is to include socially marginalized patients, who are individuals facing multiple and very challenging life circumstances such as mental health disorders, substance use disorder, and other complex issues like homelessness and involvement in criminal activities, in the target population of social nurses. This group comprises approximately 70,000 individuals in Denmark [17]. It is important to note that there is a significant utilization of healthcare services within this population, with 13% having been hospitalized in the past 3 months, and 16% having sought care from an emergency department [9]. Ultimately, it is the responsibility of the social nurse to determine whether the patient falls within the target group, resulting in a highly selected group of patients. The findings of this investigation, based on the questionnaire, will reveal whether the included patients align with the description that constitutes the target population of social nurses.

The study inclusion criteria for patients seen by a social nurse:Patients aged 18 years or olderPatients able to comply with study proceduresPatients able to understand Danish and provide informed consent

Exclusion criteria:Patients without a Danish civil registration number

The exclusion of patients without Danish civil registration numbers is because they only have access to acute medical care and cannot be followed up via the nationwide Danish health registries.

This study is conducted in accordance with ethical principles derived from international guidelines, including the Helsinki Declaration [9]. All participants will have to provide written informed consent.

The study protocol received approval from the Regional Ethics Committee (H-20031386, December 10, 2020) and is registered on ClinicalTrials.gov (reference NCT04754308, February 12, 2021). The collection and processing of data have been authorized by the Capital Region on behalf of the Danish Data Agency (P-2020-137).

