### Methods

The social nurses are instructed to invite consecutively all eligible patients who fulfill the following inclusion criteria: Patients aged 18 years or older, patients able to comply with study procedures, and patients able to understand Danish.

Recruitment to the study: The social nurse is informed about the admission of an individual socially marginalized patient either by hospital staff, when personally visiting the hospital departments, through telephone or patient record software, by external collaborators (e.g., substance maintenance clinics, shelters, street nurses, etc.), and/or when a patient directly contacts the social nurse.

Social nurses invite all eligible patients to participate in the study. After providing written informed consent, they interview the patients about alcohol and substance use, housing conditions, education, employment, and about respiratory symptoms, especially COPD symptoms (see Supplement for details).

Next, a spirometry is conducted by the social nurse to detect possible obstructive and/or impaired lung function (Fig. 1). It is performed using the NuvoAir device [18] corded to a smartphone/tablet with the app AIR MD. The guidelines recommend that spirometry be performed both before and after the administration of bronchodilator medications. However, due to practical reasons, the study procedure only includes post-bronchodilator spirometry, although it differs from the standard diagnostic practice. A standard dose of short-acting β2-agonist will be administered prior to spirometry.

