### Outcome measures

From the baseline examination, the study will report the following outcome measures:Prevalence of non-reversible airflow limitation that is a post-bronchodilator FEV1/FVC ration< 0.70Proportion of diagnosed vs. undiagnosed COPD at the time of screening (with a previous diagnosis of COPD defined as a patient-reported diagnosis in the baseline questionnaire)Proportion of patients diagnosed with lung function impairment (FEV1/FVC ratio < 0.7) subsequently examined at a respiratory outpatient clinic/GP within 4 months from screening.Prevalence of patients diagnosed with COPD after screening (identified by ICD10 code J44, or redeemed prescriptions of COPD treatment)Prevalence of participating current smokers who wish to stop smoking (patient-reported outcome in the baseline questionnaire)Prevalence of patients with identified lung function impairment (FEV1/FVC ratio < 0.7) at screening, who have a desire to quit smoking (patient-reported outcome in the baseline questionnaire)Prevalence of patients who want to quit smoking (patient-reported outcome in the baseline questionnaire) and accept the smoking cessation support offers (identified by social nurse notes in patient report).

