## Discussion

Our study is a pragmatic clinical study involving a marginalized patient population that is often excluded from participating in clinical trials due to lower health literacy and marginalization [23].

A potential methodological limitation in this study is the possibility of measurement errors arising from the use of social nurses rather than nurses with specialized respiratory training to conduct spirometry. To mitigate these risks, training is provided through local respiratory medical staff. Additionally, the social nurses are also required to be familiar with the Danish standard for lung function testing [24]. Moreover, social nurses interact directly with five to eight patients during a day shift, based on a subjective assessment of which patients need the most attention. This results in a carefully selected group of marginalized patients, potentially introducing selection bias between the study sites.

Furthermore, the handheld technical equipment used for performing the lung function test may increase the risk of measurement errors. Hence, we cannot make a definite diagnosis of COPD, but detect a possible impairment or obstructive pattern in the spirometric values. When suspicion of lung disease arises, patients undergo the standard diagnostic procedure at the current hospital, with some patients assessed in the outpatient clinic and others referred to their general practitioner. Since we cannot retrieve diagnosis from general practitioners, diagnosis verification is only available for those who attend the outpatient clinic. The five-year follow-up will determine if patients receive regular prescribed medication, facilitating confirmation of the COPD diagnosis.

We employ post-BD spirometry utilizing airflow limitation as the criterion for COPD diagnosis. Although COPD is the predominant cause of irreversible airflow limitation, it is noteworthy that a minority of patients, including those with conditions such as bronchiectasis, cannot be entirely ruled out from our study cohort. Further, an essential consideration involves the exclusion of individuals with severe, acute illnesses from the assessment of COPD prevalence due to their inability to actively participate in lung function measurements.

A strength of the study is the use of a multi-centre design on a national level, which thus with a high degree of validity reflects this subgroup of the Danish population.

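### The outcome of COPD diagnosed after screening accepts prescriptions for any inhaled medicine, with no stated link to the screening spirometry and nothing to separate asthma from COPD

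*Protocol article*

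**What the plan says.** The rule appears in two places in the protocol article.

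- **Outcome measures** lists "Prevalence of patients diagnosed with COPD after screening (identified by ICD10 code J44, or redeemed prescriptions of COPD treatment").
- **Clinical variables**, for the 5-year follow-up, says that these patients are "identified either through the National Patient Health registry based on the ICD10 code J.44 or by examining prescriptions". It then defines COPD medication so that every inhaled product is included: "by examining prescriptions for COPD medication (including all types of inhalation medicine").

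A neighbouring item under Outcome measures carries an explicit spirometric condition: "Proportion of patients diagnosed with lung function impairment (FEV1/FVC ratio < 0.7) subsequently examined". The diagnosis outcome carries none.

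On who can enter the count, the age criterion is "Patients aged 18 years or older" (Methods), and the only exclusion criterion is "Patients without a Danish civil registration number" (Study subjects).

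The Discussion explains why prescriptions are used: diagnoses made in general practice cannot be retrieved. It adds: "The five-year follow-up will determine if patients receive regular prescribed medication, facilitating confirmation of the COPD diagnosis".

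**The concern.** Inhaled medicines are not specific to COPD. Relievers and inhaled corticosteroids are also asthma treatments, and the rule takes in all of them. Nothing else in the design removes asthma. It is not an exclusion criterion, adults are eligible from 18, and only post-bronchodilator spirometry is done, so the study holds no reversibility measurement of its own.

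The screening pathway can itself produce such cases. Participants are referred when FEV1 or FVC is below 80% of predicted, even with a normal ratio, and whether or not they already have lung disease. If the work-up finds asthma and an inhaler is prescribed, the outcome as written records COPD.

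At stake is the measure of whether screening leads to a diagnosis, which bears on the second objective. The prescription arm matters most for patients managed in general practice. Without a hospital J44 code, it is their only route to confirmation. Reporting is also to be stratified by confirmed and non-confirmed diagnosis (Five-year follow-up outcome measures). If the same rule decides who is confirmed, the misclassification carries over.

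**Working it through.** **1. The text side by side**

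| Feature | Outcome measures | Clinical variables | Discussion |
|---|---|---|---|
| Link between arms | J44 or prescriptions | J44 or prescriptions | prescriptions help confirm |
| Drug class | COPD treatment | all inhaled medicine | not given |
| Number or regularity | uncounted plural | uncounted plural | regular |
| Screening FEV1/FVC | not named here; named for neighbouring items | not named for this outcome | context is patients with suspected lung disease |
| Asthma | not addressed | not addressed | not addressed |

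Clinical variables also defines a group without COPD as determined by screening. Nothing in the rule keeps members of that group from being counted later through the prescription arm.

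**2. The plan's own figure**

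The only calculated figure is N = 511 (Study design), for 8.6% (twice 4.3%) against 4.3%, with 80% power and alpha 0.05. A two-sided, two-sample comparison with pooled null variance gives, per group:

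n = [1.960·√(2·0.0645·0.9355) + 0.842·√(0.043·0.957 + 0.086·0.914)]² / 0.043² = 511.1

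The unpooled version gives 508.4, or 509 rounded up. So 511 reproduces. It concerns baseline prevalence, which Clinical variables builds from screening spirometry plus self-report. The disputed rule does not enter it.

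**3. Illustration of size**

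Inputs: N = 511 (document); p, the true COPD share, taken as 8.6% (the planning value) and, as an assumption, 30%; f, the share of participants without COPD who meet the prescription arm, assumed at 2% to 20% because the documents give no figure. Every true case is assumed to be counted, and the rule is applied to the whole cohort.

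- False cases = N·(1 − p)·f
- Observed proportion = p + (1 − p)·f
- Share of counted cases that are true = p / observed proportion

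At p = 8.6%: 511 × 0.086 ≈ 44 with COPD, and 511 − 44 = 467 without.

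| f | False cases | Observed | True share of counted |
|---|---|---|---|
| 2% | 467 × 0.02 ≈ 9 | 10.4% | 82% |
| 5% | 467 × 0.05 ≈ 23 | 13.2% | 65% |
| 10% | 467 × 0.10 ≈ 47 | 17.7% | 48% |
| 20% | 467 × 0.20 ≈ 93 | 26.9% | 32% |

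At p = 30%: 511 × 0.30 ≈ 153 with COPD and 358 without. The same range of f adds about 7 to 72 false cases, the observed proportion runs from 31.4% to 44.0%, and the true share of counted cases from 96% to 68%. The relative inflation shrinks; its direction does not change.

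**The case against.** Much of the opposing case is fair.

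- **Detail left to other documents.** A minimum number of redemptions, drug code lists and asthma-code handling commonly sit in a full protocol or SAP. Their absence alone would be no finding. What remains is what the article does fix: an either/or rule that expressly admits every inhaled medicine.
- **One redemption.** A reader might infer that a single redemption is enough. The documents do not say so. Both statements use an uncounted plural, and the Discussion speaks of regular medication. All that can be said is that no minimum is stated. A count alone would not cure the problem either, since a person with asthma may redeem inhalers regularly.
- **Whole cohort.** That the rule applies whatever the spirometry showed is read from a missing condition, and the Discussion mentions prescriptions while describing patients with suspected lung disease. The contrast with neighbouring outcomes that do name the ratio supports the whole-cohort reading but does not settle it.
- **Bronchiectasis.** Naming this condition and not asthma might look like an oversight. That sentence concerns causes of irreversible airflow limitation, gives an example only, and says nothing about the prescription rule.
- **Weight of the outcome.** It is one descriptive outcome among several. J44 confirmation is also collected from hospital records, and the Discussion says that prescriptions help confirmation, not that they suffice. This limits the consequence, but the outcome definition itself still makes prescriptions sufficient.

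**Conclusion.** The point holds as a badly fixed outcome definition. Followed as written, it can count people with asthma and other inhaler users as COPD diagnosed after screening, and this lack of specificity pushes the reported yield upward. The uncounted rule also needs reconciling with the regular medication expected in the Discussion.

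The size cannot be derived from the documents. The range of about 9 to 93 false cases rests on an assumed 2% to 20% among 467 participants and on applying the rule to the whole cohort. At a true prevalence of 30% it becomes about 7 to 72.

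Two stronger readings are not supported. A reader might set these counts against the 44 expected cases and conclude that the false cases rival the true ones. But 44 is the planned baseline prevalence, which includes self-reported earlier diagnoses; it is not a forecast of new diagnoses, and the Introduction hypothesises at least a doubling, so 8.6% is a lower bound. A reader might also infer that the prevalence comparison or the sample size is compromised. Both use the baseline definition and are unaffected.

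**What to change.** - Make the primary version of this outcome a J44 code, or repeated redemptions of maintenance inhaled medication within a set window, among participants with screening FEV1/FVC below 0.70. State the number and the window, so that Outcome measures and Clinical variables agree with the Discussion.
- Do not count prescription-only cases that have a register asthma code (J45/J46) and no J44.
- Report J44-confirmed and prescription-only cases separately, and state whether the same rule decides the confirmed and non-confirmed strata.
- Keep the present any-inhaler rule in the whole cohort as a sensitivity analysis.

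This is a classification rule for register data and has no bearing on treatment. Maintenance medication is preferred to one named drug class because a single class would miss COPD treated with other maintenance inhalers.

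The cost is outcome wording and code lists; the patient and prescription registers are already planned for linkage. The downside is that some true COPD is missed: patients treated only with relievers, those with a false-negative handheld spirometry, and those with no usable test. Participants referred only for a low FEV1 or FVC also leave the primary version. Asthma managed only in general practice stays partly undetected, because those diagnoses cannot be retrieved. The sensitivity analysis shows how far the choice of rule matters.

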### Statistical considerations

Continuous variables will be presented as mean with standard deviation if the variable can be assumed to be normally distributed, otherwise, the median and interquartile range will be presented. Categorical variables will be presented with frequencies for each level and their corresponding percentages.

The prevalence of COPD in the study population will be compared to the prevalence in the Danish general population using an unadjusted test of the ratio of proportions, with a normal approximation of the logarithm of the ratio.

Since participants can die or otherwise drop out during the follow-up period, participants contribute with different follow-up lengths. The number of contacts in the follow-up period will therefore be reported as a rate (contact rate) of the number of contacts divided by the follow-up length, that is as contacts per year.

The healthcare contact rate will be compared among the three previously described COPD groups: undiagnosed COPD at inclusion who underwent further assessment, undiagnosed COPD without further assessment, and previously diagnosed COPD at inclusion, using a Poisson regression model. The model will include potential confounders as independent variables in addition to the COPD groups.

Sub-analyses for the rate of acute contacts and outpatient contacts will be conducted using models constructed in the same way as for all contacts.

Medication usage as a rate: number of prescriptions per year. Likewise, a Poisson regression model will be used to compare the rates among the COPD groups. However, the groups will be divided into no COPD versus diagnosed COPD. We will employ rigorous control for potential confounders. Specifically, age, smoking history, and comorbidities will be included as covariates in our models.

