### Study design

This is a prospective longitudinal study with 5 years follow-up from the date of inclusion.

The power calculation is based on the assumption that the prevalence of COPD will be twice the prevalence in the Danish background population (4.3%). With a power of 80% and a significance level of 0.05, a sample comprising 511 patients is required.

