#### Five-year follow-up outcome measures

At follow-up, we will report on whether:Opportunistic screening for COPD by social nurses has an impact on the rate of hospital contacts. This is assessed by examining the number of hospital contacts per person year within each year of the 5-year follow-up (both outpatient visits and hospitalizations) with a diagnosis related to COPD for three patient groups: (1) the group with no previous COPD diagnosis, impaired lung function at screening, and who underwent further assessment, (2) the group of patients with previous diagnosed COPD and impaired lung function at screening, and (3) the group with no previous COPD diagnosis, impaired lung function at screening, and who declined further assessment (Fig. 1).Opportunistic screening for COPD by social nurses has an impact on the use of COPD medication. This is assessed by examining number of prescriptions filled for COPD medications for two patient groups: (1) the group with no previous COPD diagnosis, impaired lung function at screening, and who underwent further assessment, and (2) the group of patients with previous diagnosed COPD at (Fig. 1). The reporting of medication will be organized into distinct categories, encompassing bronchodilators, corticosteroids, rescue medications, and maintenance therapies. Within each of these groups, the dosage prescribed or dispensed will be quantified.

Previous or no previous COPD diagnosis is assessed by the questionnaire at the time of screening as a patient-reported outcome. The lung function impairment is defined as FEV1/FVC ratio < 0.7. In the reporting, patients are stratified into groups with confirmed and non-confirmed COPD diagnosis.

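### Hospital contacts and prescriptions are to be compared by Poisson regression with no provision for overdispersion, so model-based standard errors are likely to be too small

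*Protocol article*

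**What the plan says.** The Statistical considerations section of the protocol article compares the contact rate among three COPD groups (undiagnosed with further assessment, undiagnosed without it, previously diagnosed) "using a Poisson regression model. The model will include potential confounders as independent variables in addition to the COPD groups".

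The same choice carries over to the other follow-up analyses:
- Acute and outpatient contacts: "Sub-analyses for the rate of acute contacts and outpatient contacts will be conducted using models constructed in the same way as for all contacts".
- Prescriptions per year: "Likewise, a Poisson regression model will be used to compare the rates among the COPD groups". The contrast changes here: "However, the groups will be divided into no COPD versus diagnosed COPD".

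The named adjustment is that "age, smoking history, and comorbidities will be included as covariates in our models". Unequal follow-up is handled by dividing each person's count by that person's follow-up time.

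On the outcome itself, Clinical variables states: "The utilization of healthcare services is evaluated based on all hospital contacts, including outpatient visits, admissions, and emergency department (ED) visits". Five-year follow-up outcome measures is narrower. It restricts contacts to those with a COPD-related diagnosis and looks at the "number of hospital contacts per person year within each year of the 5-year follow-up".

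The article does not say how standard errors are obtained. It gives no mean, variance or dispersion for any count.

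**The concern.** Poisson regression takes the variance of each count to equal its mean, given the covariates. These counts are unlikely to behave that way. One admission tends to lead to outpatient visits, and maintenance treatment produces repeat prescriptions. Participants differ widely in housing, substance use, mental illness and use of services. Housing and substance use are recorded at baseline but are not among the three covariates named. Dividing by follow-up time corrects for unequal exposure and does nothing about extra variance.

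If the variance exceeds the mean, the rate ratios can still be estimated properly, but their model-based standard errors are too small. The second objective, the 5-year impact of screening, rests on these models for hospital contacts and medication. A difference between patients who were assessed and those who declined could look statistically firm when it is within chance variation, and it would then be read as an effect of screening.

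**Working it through.** **The plan's own figure.** The article gives no design figure for the Poisson analyses. Its only one, 511 patients, belongs to the prevalence comparison. The two-sided pooled two-proportion formula with 4.3% against 8.6%, alpha 0.05 and power 80% gives 512 per group, so 511 reproduces to within rounding. It has no bearing on the count models.

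**Inputs.** From the article: Poisson regression, a three-group comparison for contacts, a two-group comparison for prescriptions, and 5 years of follow-up. The significance level of 0.05 is stated for the sample size and is assumed to apply here too. The dispersion φ (residual variance divided by mean, after covariates) is not in the documents and is shown as a range.

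**Formulas.** If the variance is φ times the mean, then:
- the true standard error is √φ times the Poisson standard error;
- for two groups, the type I error of a nominal 5% test is 2 × [1 − Φ(1.96/√φ)];
- for the three-group 2-df test, it is exp(−5.991/(2φ)).

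**Example, φ = 2.** √2 = 1.41. For two groups, 1.96/1.41 = 1.39, which gives 17%. For three groups, exp(−5.991/4) = exp(−1.498), which gives 22%.

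| φ (assumed) | SE too small by a factor of | Type I error, two groups | Type I error, three groups (2 df) | True coverage of a 95% interval for one contrast |
|---|---|---|---|---|
| 1 | 1.00 | 5% | 5% | 95% |
| 1.5 | 1.22 | 11% | 14% | 89% |
| 2 | 1.41 | 17% | 22% | 83% |
| 3 | 1.73 | 26% | 37% | 74% |
| 5 | 2.24 | 38% | 55% | 62% |

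The last column is 100% minus the two-group error.

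**What produces such values of φ.** If persons' underlying rates vary as a gamma distribution with relative variance α, then φ = 1 + αμ, where μ is the expected count per person over follow-up. With α = 1 (assumed), an average of 0.5 contacts over 5 years gives φ = 1.5, and an average of 4 gives φ = 5. So rare events bring little overdispersion and frequent events bring much.

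**Simulation check.** Three groups of 60 (assumed), no true difference, up to 5 years of follow-up, no covariates, 500 runs per scenario, 2-df test:

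| Contacts per year (assumed) | α (assumed) | φ observed | Type I error, Poisson | Type I error, robust |
|---|---|---|---|---|
| 0.5 | 0.5 | 2.0 | 24% | 6% |
| 1 | 0.5 | 3.1 | 42% | 6% |
| 1 | 1 | 5.1 | 59% | 5% |
| 1 | 2 | 9.0 | 75% | 6% |

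With no extra heterogeneity (α = 0), Poisson rejected in 4–8% of runs across rates of 0.5 to 4 per year. The simulation agrees with the 2-df formula to within a few points and shows that a robust variance brings the error back close to 5%.

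**The case against.** The strongest reply is that this is a condensed article. Naming a Poisson model does not exclude robust or scaled standard errors, and an analysis plan that is not shown may provide them. That is fair as far as it goes: the text neither plans nor rules them out, so it cannot be said that uncorrected errors will be used. But the article does more than stay silent. It chooses the model family and applies it to every follow-up comparison, and that choice, followed as written, suits these data poorly.

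Several narrower objections stand and limit the point:
- A reader might infer that standard errors will certainly be far too small, with error rates of 60% or more. The documents do not support this. They give no dispersion, and the high figures need frequent contacts and strong heterogeneity. The outcome section counts only COPD-related contacts, which may be much rarer than all contacts.
- The planned covariates will absorb some between-person variance. The φ in the first table is what remains after adjustment, whereas the simulation had no covariates.
- A reader might infer that five correlated yearly counts per person will be modelled. The statistical section defines one rate per person over the whole follow-up. The yearly wording may only describe reporting.
- For COPD prescriptions in people without COPD against people with diagnosed COPD, a true difference is expected. False positives are therefore not the main risk there; intervals that are too narrow are.
- Adding hospital as a factor might seem a natural extension, but nothing in the documents or the calculation supports requiring it.

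**Conclusion.** The point holds in this form: Poisson regression is specified for all, acute and outpatient contacts and for prescriptions, with no provision for overdispersion, and overdispersion is likely. Its direction is certain for any residual dispersion above 1. Its size is not known. It runs from modest (φ = 1.5: two-group error 11%, three-group 14%) to severe (φ = 5: 38% and 55%), and where these data fall rests on assumption. The effect is on intervals and tests, not on the rate-ratio estimates. The prevalence comparison and the sample size of 511 are unaffected.

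**What to change.** In Statistical considerations, replace the Poisson model with one of the following, stated for all contact analyses (all, acute, outpatient) and for prescriptions:
- negative binomial regression with log follow-up time as offset; or
- Poisson regression with log follow-up time as offset and robust (sandwich) or Pearson-scaled variance.

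If the year-by-year counts in Five-year follow-up outcome measures are to be modelled, add that standard errors are clustered on person.

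The cost is a sentence or two of text and no change in data collection. Intervals will be wider, but valid. If dispersion turns out close to 1, little is lost. The change should be fixed before the follow-up outcomes are analysed.
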